| Yes                                                                                          | .                            | 2196 (57.8)                    | .                                    | 80 (42.3)                   | .                                       | 2116 (58.6)                 | -16.3 (-23.3, -9.0)         |
| Time to prior positive test (days)                                                    | 198                          | 148.0 [70.0, 204.0]            | 6                                    | 163.0 [103.0, 222.0]        | 192                                     | 148.0 [67.5, 202.0]         | 15.0 ( not defined ) |
| How do you rate your risk of being COVID-19+?                                         | 3657                         | .                              | 176                                  | .                           | 3481                                    | .                           |                             |
| High or very high                                                                            | .                            | 651 (17.8)                     | .                                    | 51 (29.0)                   | .                                       | 600 (17.2)                  | 11.7 (5.4, 18.9)            |
| Identical                                                                                    | .                            | 1249 (34.2)                    | .                                    | 69 (39.2)                   | .                                       | 1180 (33.9)                 | 5.3 (-1.8, 12.8)            |
| Low or very low                                                                              | .                            | 1757 (48.0)                    | .                                    | 56 (31.8)                   | .                                       | 1701 (48.9)                 | -17.0 (-23.7, -9.7)         |
| Emergency department discharge status****                                             | 1328                         | .                              | 36                                   | .                           | 1292                                    | .                           | .                           |
| Hospitalization                                                                              | .                            | 24 (1.8)                       | .                                    | 2 (5.6)                     | .                                       | 22 (1.7)                    | 3.9 (-0.3, 16.5)            |
| Only emergency department visit: outpatients                                                 | .                            | 1304 (98.2)                    | .                                    | 34 (94.4)                   | .                                       | 1270 (98.3)                 | -3.9 (-16.5, 0.3)           |
| Among patients with rapid multiplex respiratory virus test, other respiratory viruses | 581                          | .                              | 116                                  | .                           | 465                                     | .                           | .                           |
| Yes*****                                                                                     | .                            | 77 (13.3)                      | .                                    | 5 (4.3)                     | .                                       | 72 (15.5)                   | -11.2 (-15.7, -5.2)         |

\* Patients with indeterminate results or a known positive SARS-CoV-2 status were not included in this table. In univariate analysis, factors associated with new infections diagnosed through screening for asymptomatic/paucisymptomatic patients were mainly older age, having mild symptoms, not being from France, particularly being from Sub-Saharan Africa, being unemployed, not having medical coverage, living in a community, being a case contact and not being previously screened.

\*\* Among patients who underwent a rapid molecular SARS-CoV-2 test, 258 (7.4%) reported having symptoms. Among patients who underwent a rapid multiplex respiratory virus test, 508 (90.1%) reported having symptoms.

\*\*\* Chronic diseases: diabetes, arterial hypertension, angina pectoris, chronic bronchitis, asthma or chronic respiratory disease

\*\*\*\* For this variable of the DEPIST-COVID questionnaire, data were collected in 8 centers, and it was not possible to collect them later in the remaining 10 centers. Findings are presented for 8 centers (n=1,510 patients, missing data: 12.1% in the 8 centers).

\*\*\*\*\* Rhinovirus/Enterovirus: n=29 (37.7%), Coronavirus OC43: n=12 (15.6%), Coronavirus NL63: n=10 (13.0%), Human Metapneumovirus A+B: n=10 (13.0%), Respiratory Syncytial Virus A+B: n=6 (7.8%), Parainfluenza virus 3: n=3 (3.9%), Bocavirus: n=2 (2.6%), Parainfluenza virus 4: n=2 (2.6%), Bocavirus | Coronavirus HKU1: n=1 (1.3%), Coronavirus 229E: n=1 (1.3%), Influenza A: n=1 (1.3%). Among SARS-CoV-2+ patients: Rhinovirus/Enterovirus: n=2, Bocavirus: n=1, Parainfluenza virus 4: n=1, Respiratory Syncytial Virus A+B: n=1.

Q1: First quartile; Q3: Third quartile; CI: Confidence interval.

Appendix F. Figure Newly diagnosed SARS-CoV-2-positive patients per emergency department and strategy

Fig F1. Newly diagnosed SARS-CoV-2-positive patients per emergency department and strategy

[figure not shown]

Appendix G. Figure SARS-CoV-2 incidence rate in the Paris metropolitan area and per geographical department (75, 77, 92, 93, 95) of the emergency departments involved in the study

Fig G1. SARS-CoV-2 incidence rate in the Paris metropolitan area and per geographical department (75, 77, 92, 93, 95) of the emergency departments involved in the study

[figure not shown]

y.o.: years old

# Appendix H. Table Characteristics of patients newly diagnosed with SARS-CoV-2 infection

Table H1. Characteristics of patients newly diagnosed with SARS-CoV-2 infection

|                        | Total population
N=3 943 |                                | Control period
n=2 084 |                                | Intervention period
n=1 859 |                                | Risk difference  |
|------------------------|-------------------------------------|--------------------------------|-----------------------------------|--------------------------------|----------------------------------------|--------------------------------|-------------------------|
|                        | N                                   | n (%)
or median [Q1,
Q3] | n                                 | n (%)
or median [Q1,
Q3] | n                                      | n (%)
or median [Q1,
Q3] | %
or median (95% CI) |
| Age
(years) | 3943                                | 59.7 [41.0, 75.0]              | 2084                              | 61.0 [41.4, 77.0]              | 1859                                   | 58.0 [40.0, 74.0]              | 3.0 (1.0, 5.0)          |
| Sex             | 3943                                |                                | 2084                              |                                | 1859                                   |                                |                         |
| Female                 |                                     | 1845 (46.8)                    |                                   | 947 (45.4)                     |                                        | 898 (48.3)                     | -2.9 (-6.0, 0.3)        |
| Center          | 3943                                |                                | 2084                              |                                | 1859                                   |                                |                         |
| 1                      |                                     | 274 (6.9)                      |                                   | 167 (8.0)                      |                                        | 107 (5.8)                      | 2.3 (0.7, 3.8)          |
| 2                      |                                     | 197 (5.0)                      |                                   | 101 (4.8)                      |                                        | 96 (5.2)                       | -0.3 (-1.7, 1.0)        |
| 3                      |                                     | 142 (3.6)                      |                                   | 73 (3.5)                       |                                        | 69 (3.7)                       | -0.2 (-1.4, 1.0)        |
| 4                      |                                     | 282 (7.2)                      |                                   | 142 (6.8)                      |                                        | 140 (7.5)                      | -0.7 (-2.4, 0.9)        |
| 5                      |                                     | 454 (11.5)                     |                                   | 261 (12.5)                     |                                        | 193 (10.4)                     | 2.1 (0.1, 4.1)          |
| 6                      |                                     | 194 (4.9)                      |                                   | 90 (4.3)                       |                                        | 104 (5.6)                      | -1.3 (-2.7, 0.08)       |
| 7                      |                                     | 313 (7.9)                      |                                   | 181 (8.7)                      |                                        | 132 (7.1)                      | 1.6 (-0.1, 3.3)         |
| 8                      |                                     | 300 (7.6)                      |                                   | 114 (5.5)                      |                                        | 186 (10.0)                     | -4.5 (-6.2, -2.9)       |
| 9                      |                                     | 259 (6.6)                      |                                   | 168 (8.1)                      |                                        | 91 (4.9)                       | 3.2 (1.6, 4.7)          |
| 10                     |                                     | 216 (5.5)                      |                                   | 92 (4.4)                       |                                        | 124 (6.7)                      | -2.3 (-3.7, -0.8)       |
| 11                     |                                     | 132 (3.3)                      |                                   | 59 (2.8)                       |                                        | 73 (3.9)                       | -1.1 (-2.3, 0.03)       |
| 12                     |                                     | 217 (5.5)                      |                                   | 123 (5.9)                      |                                        | 94 (5.1)                       | 0.8 (-0.6, 2.3)         |
| 13                     |                                     | 180 (4.6)                      |                                   | 93 (4.5)                       |                                        | 87 (4.7)                       | -0.2 (-1.5, 1.1)        |
| 14                     |                                     | 205 (5.2)                      |                                   | 104 (5.0)                      |                                        | 101 (5.4)                      | -0.4 (-1.9, 0.9)        |
| 15                     |                                     | 99 (2.5)                       |                                   | 19 (0.9)                       |                                        | 80 (4.3)                       | -3.4 (-4.5, -2.4)       |
| 16                     |                                     | 101 (2.6)                      |                                   | 74 (3.6)                       |                                        | 27 (1.5)                       | 2.1 (1.1, 3.1)          |
| 17                     |                                     | 231 (5.9)                      |                                   | 123 (5.9)                      |                                        | 108 (5.8)                      | 0.09 (-1.4, 1.6)        |
| 18                     |                                     | 147 (3.7)                      |                                   | 100 (4.8)                      |                                        | 47 (2.5)                       | 2.3 (1.1, 3.5)          |

Q1: First quartile; Q3: Third quartile; CI: Confidence interval.

# Appendix I. Primary outcome modeling, sensitivity analyses, and intercluster and intracluster correlation coefficients

## 1. Final model

The following models were compared using likelihood ratio tests:

- A model including the center as a random intercept, the center-by-weekly period interaction as a random effect, as well as the strategy (intervention vs. control) and the weekly period as fixed effects.
- A model including the same variables (Model a) and the community incidence rate for SARS-CoV-2 as a fixed effect.
- A model including the same variables (Model b) and the community incidence rate-by-weekly period interaction.

The selected model was **Model c**.

Table I1. Coefficient estimates from the generalized linear mixed model with a Poisson distribution including the center as a random intercept, the center-by-weekly period interaction as a random effect and the strategy, weekly period and community incidence rate-by-weekly period interaction as fixed effects (SAS PROC Glimmix)

| Variable                                              | Coefficient | Standard error | t test | p value | Relative risk | (95% Confidence interval)
relative risk |
|-------------------------------------------------------|-------------|----------------|--------|---------|---------------|--------------------------------------------|
| Strategy                                              | 0.02        | 0.04           | 0.48   | 0.63    | 1.02          | (0.94 to 1.11)                             |
| Weekly period                                         | -0.09       | 0.02           | -4.45  | <.0001  |               |                                            |
| Community incidence rate                              | 0.00        | 0.00           | -0.75  | 0.46    |               |                                            |
| Community incidence rate-by-weekly period interaction | 0.00        | 0.00           | 5.33   | <.0001  |               |                                            |

  

| Covariance                   | Coefficient | Standard error |
|------------------------------|-------------|----------------|
| Center                       | 0.07        | 0.03           |
| Center-by-period interaction | 0.00        | 0.00           |

The variability among centers was estimated as small (0.07) compared to the associated standard error (0.03).

The ratio of the 'Generalized Chi-Square statistic' and its degrees of freedom was 1.17 and close to 1. The scaled Pearson statistic for the conditional distribution was similar (1.17). These arguments are not in favour of an overdispersion of the data.

Significant weekly period effect ( $p < 0.0001$ ) and community incidence rate-by-weekly period interaction ( $p < 0.0001$ ) were identified.

Table I2. Significant random effects

| Variable                     | Center    | Coefficient | Standard error | t test | p value |
|------------------------------|-----------|-------------|----------------|--------|---------|
| Intercept                    | Center 1  | -0.36       | 0.14           | -2.61  | 0.01    |
| Center-by-period interaction | Center 11 | 0.05        | 0.02           | 2.48   | 0.02    |
| Intercept                    | Center 13 | 0.30        | 0.15           | 2.02   | 0.05    |
| Intercept                    | Center 5  | 0.31        | 0.14           | 2.17   | 0.04    |
| Intercept                    | Center 6  | 0.33        | 0.13           | 2.59   | 0.01    |
| Intercept                    | Center 8  | -0.37       | 0.14           | -2.72  | 0.01    |

According to the random parameters of the final model, the intracluster variability was not negligible. Significant differences were observed in 5 centers. Given the multiplicity of the tests, the interpretation is limited.

## 2. Sensitivity analyses

Table I3. Analysis considering a binarized period (0/1)

| Variable     | Coefficient | Standard error | t test | p value | Relative risk | (95% Confidence interval)
relative risk |
|--------------|-------------|----------------|--------|---------|---------------|--------------------------------------------|
| Intervention | -0.02       | 0.07           | -0.25  | 0.80    | 0.98          | (0.84 to 1.15)                             |

  

| Covariance                   | Coefficient | Standard error |
|------------------------------|-------------|----------------|
| Center                       | 0.08        | 0.04           |
| Center-by-period interaction | 0.03        | 0.02           |

Table I4. Analysis including variables used for randomization (screening equipment in emergency departments and flow in emergency departments)

| Variable     | Coefficient | Standard error | t test | p value | Relative risk | (95% Confidence interval)
relative risk |
|--------------|-------------|----------------|--------|---------|---------------|--------------------------------------------|
| Intervention | 0.02        | 0.04           | 0.53   | 0.60    | 1.02          | (0.94 to 1.11)                             |

  

| Covariance                   | Coefficient | Standard error |
|------------------------------|-------------|----------------|
| Center                       | 0.06        | 0.03           |
| Center-by-period interaction | 0.00        | 0.00           |

Table I5. Analysis including strategy \* week\_since\_roll\_out interaction

| Variable                     | Coefficient | Standard error | t test         | p value | Relative risk | (95% Confidence interval)
relative risk |
|------------------------------|-------------|----------------|----------------|---------|---------------|--------------------------------------------|
| Intervention                 | -0.02       | 0.07           | -0.28          | 0.78    | 0.98          | (0.85 to 1.13)                             |
|                              |             |                |                |         |               |                                            |
| Covariance                   |             | Coefficient    | Standard error |         |               |                                            |
| Center                       |             | 0.07           | 0.03           |         |               |                                            |
| Center-by-period interaction |             | 0.00           | 0.00           |         |               |                                            |

Table I6. Analysis at the center level

| Model                   | Coefficient | Standard error | t test | p value | Relative risk | (95% Confidence interval)
relative risk |      |
|-------------------------|-------------|----------------|--------|---------|---------------|--------------------------------------------|------|
| Final model             | 0.02        | 0.04           | 0.48   | 0.63    | 1.02          | 0.94                                       | 1.11 |
| Model without center 1  | 0.04        | 0.04           | 0.92   | 0.36    | 1.04          | 0.96                                       | 1.14 |
| Model without center 2  | 0.02        | 0.04           | 0.39   | 0.70    | 1.02          | 0.93                                       | 1.11 |
| Model without center 3  | 0.02        | 0.04           | 0.52   | 0.60    | 1.02          | 0.94                                       | 1.11 |
| Model without center 4  | 0.01        | 0.04           | 0.23   | 0.82    | 1.01          | 0.93                                       | 1.10 |
| Model without center 5  | 0.00        | 0.04           | -0.05  | 0.96    | 1.00          | 0.91                                       | 1.09 |
| Model without center 6  | 0.04        | 0.04           | 0.81   | 0.42    | 1.04          | 0.95                                       | 1.13 |
| Model without center 7  | 0.01        | 0.04           | 0.29   | 0.77    | 1.01          | 0.93                                       | 1.10 |
| Model without center 8  | -0.01       | 0.05           | -0.25  | 0.80    | 0.99          | 0.90                                       | 1.08 |
| Model without center 9  | 0.04        | 0.04           | 0.82   | 0.41    | 1.04          | 0.95                                       | 1.13 |
| Model without center 10 | 0.02        | 0.04           | 0.38   | 0.71    | 1.02          | 0.93                                       | 1.11 |
| Model without center 11 | 0.03        | 0.04           | 0.71   | 0.48    | 1.03          | 0.95                                       | 1.13 |
| Model without center 12 | 0.02        | 0.04           | 0.44   | 0.66    | 1.02          | 0.94                                       | 1.11 |
| Model without center 13 | 0.03        | 0.04           | 0.68   | 0.50    | 1.03          | 0.94                                       | 1.12 |
| Model without center 14 | 0.02        | 0.04           | 0.46   | 0.64    | 1.02          | 0.93                                       | 1.12 |
| Model without center 15 | 0.00        | 0.04           | 0.02   | 0.98    | 1.00          | 0.92                                       | 1.09 |
| Model without center 16 | 0.03        | 0.04           | 0.69   | 0.49    | 1.03          | 0.95                                       | 1.12 |
| Model without center 17 | 0.02        | 0.04           | 0.42   | 0.67    | 1.02          | 0.93                                       | 1.11 |
| Model without center 18 | 0.03        | 0.04           | 0.76   | 0.45    | 1.03          | 0.95                                       | 1.13 |

A sensitivity analysis was performed at the center level, successively excluding one center from the sample and estimating the parameters of the 18 samples. No center influenced the estimation of the strategy fixed parameter of the model; the response to the intervention did not vary.

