### 13.2 Description of the statistical methods

The analysis will be performed at the end of the research, after a data review meeting and freezing of the database. An analysis plan will be drafted and any changes will be documented.

The characteristics of the sites and patients will be described. The proportion of patients tested positive for other respiratory viruses will be described. Qualitative data will be described by means of numbers and proportions, and quantitative variables will be described using means, standard deviations, ranges, medians and interquartile ranges.

The primary analysis will be performed according to the intent-to-treat (ITT) principle. The primary outcome will be analysed using a generalised linear mixed model (Poisson distribution or any other distribution adapted to the data) with the strategy as a fixed effect, the centre x strategy interaction as a random effect and the centre as a random intercept.

For the other secondary outcomes:

- The proportion of patients tested positive for SARS-CoV-2 among the asymptomatic patients tested and that in the Paris Metropolitan area at the same period will be compared using an asymptotic Wald test.  
The proportion obtained in each emergency department will be compared to that of the department's IRIS geographical area using an asymptotic Wald test.  
The same comparisons will be made among the symptomatic patients tested and across the entire tested population.
- The feasibility of the testing will be described: proportion of patients who have completed the questionnaire, proportion of offered, accepted and performed tests, and notified of the SARS-CoV-2 result and staff involved (nurses, caregivers, doctors, others),
- The proportion of patients tested positive for SARS-CoV-2 among the patients tested, the proportion of asymptomatic patients among the patients tested and the proportion of asymptomatic patients among the patients tested positive for SARS-CoV-2 will be described in the 2 strategies.
- The symptoms of patients tested positive for SARS-CoV-2 will be described in both strategies and in the total population.

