## Changes to the analysis plan

### **Primary endpoint analysis**

The primary outcome will be analysed using a generalised linear mixed model (Poisson distribution or any other distribution adapted to the data) with the centre as a random intercept, the centre-by-period interaction as random effect and the strategy, the period and the incidence rate-by-period interaction as fixed effects. The logarithm of the number of patients will be included as an offset term in the model.

The period will be modelled as weekly (1 to 15).

Patients considered non-positive for SARS-CoV-2 will be patients not tested, patients tested negative or with an undeterminate result and patients tested positive with a known SARS-CoV2+ status for less than 3 months.

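### Leave-one-out stability shows that no single centre drives the pooled relative risk; it does not show that the response to screening was the same in all centres

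*Combined protocol and SAP*

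**What the plan says.** Appendix I, section 2, describes a centre-level sensitivity analysis, "successively excluding one center from the sample and estimating the parameters of the 18 samples". Table I6 prints the pooled strategy coefficient from each refit. The lowest estimate is "Model without center 8 | -0.01 | 0.05 | -0.25 | 0.80 | 0.99" and the highest is "Model without center 1 | 0.04 | 0.04 | 0.92 | 0.36 | 1.04" (the refits without centres 6 and 9 also give 1.04). The text concludes: "No center influenced the estimation of the strategy fixed parameter of the model; the response to the intervention did not vary".

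The models that bear on this question differ across the documents:

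- Protocol 13.2 planned the strategy as a fixed effect, with "the centre x strategy interaction as a random effect and the centre as a random intercept".
- Final SAP, section 1.1 (primary endpoint): centre as a random intercept; strategy, period and period-by-strategy as fixed effects. There is no centre-by-strategy term.
- Changes to the analysis plan (primary endpoint): "the centre-by-period interaction as random effect" is added, with period in weeks and an incidence-by-period term. There is no centre-by-strategy term.
- Appendix I, section 1: the fitted model follows that last specification.

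Section 1.5 of the final SAP, which summarises the changes, mentions the fixed period-by-strategy term. It does not mention the loss of the centre-by-strategy random effect.

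**The concern.** Influence and heterogeneity are different questions. Leave-one-out asks whether the average depends on one centre. Whether centres responded differently needs a variance component for the strategy effect, centre-specific estimates or a heterogeneity test, and Appendix I reports none of these. The term that would have supplied the answer was planned and then left out.

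An average RR near 1 with the same response everywhere is a different finding from an average RR near 1 with gains in some departments and none in others. A department deciding whether to adopt nurse-driven screening would read the two differently. If real variation in response is left out of the error structure, the interval for the average effect could also be too narrow.

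**Working it through.** **Inputs.** Final model: coefficient 0.02, SE 0.04, RR 1.02 (0.94 to 1.11), Table I1. Binarized-period model: coefficient -0.02, SE 0.07, RR 0.98 (0.84 to 1.15), with "Center-by-period interaction | 0.03 | 0.02" as variance and SE, Table I3. New diagnoses by centre and period: Table H1. Period lengths: Table C1. Diagnoses through nurse screening by centre: Table J2.

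**1. Reproducing the printed intervals.** With exp(b ± q × SE):
- Final model, b = 0.0206 and SE = 0.043 (both within rounding), q = 1.96: 1.02 (0.94 to 1.11), as printed.
- Table I3, printed b and SE, q = 1.96: 0.98 (0.85 to 1.12). With b = -0.0175, SE = 0.0749 (both within rounding) and a t quantile on 16 df: 0.98 (0.84 to 1.15), as printed.

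**2. What leave-one-out can detect.** With 18 equally weighted centres, removing one with relative risk r changes the pooled log RR by -ln(r/1.02)/17.
- r = 1.6: pooled RR = exp(0.0198 - 0.0265) = 0.99.
- r = 0.7: pooled RR = exp(0.0198 + 0.0221) = 1.04.
- r = 0.6: pooled RR = exp(0.0198 + 0.0312) = 1.05.

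The whole span of Table I6 is 0.99 to 1.04. It is therefore compatible with individual centres well away from 1.

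**3. What Table I3 allows.** If 0.03 is the variance of each centre-period effect, the contrast of a centre's two periods has variance 2 × 0.03 = 0.06 and SD 0.245. The 95% range is 0.98 × exp(±1.96 × 0.245) = 0.61 to 1.58. If 0.03 is instead the variance of a centre-specific period slope, the SD is 0.173 and the range is 0.70 to 1.38.

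The printed SE helps to choose between the two. The mean count per centre-period is 3943/36 = 109.5.
- First reading: sqrt(2 × (0.03 + 1/109.5)/18) = 0.066.
- Slope reading: sqrt((0.03 + 2/109.5)/18) = 0.052.

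Weighting by the actual counts gives 0.067 and 0.053. The printed value is 0.07, so the first reading fits better.

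**4. Precision of that variance.** 0.03/0.02 = 1.5, and the Wald interval is 0.03 ± 1.96 × 0.02 = -0.01 to 0.07, which includes zero.

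**5. Raw centre ratios.** These assume equal adult visits per day in both periods of a centre, because visit counts by centre and period order are not given.
- Centre 16: (27/35)/(74/35) = 0.36. Centre 15: (80/40)/(19/40) = 4.21. Across the 18 centres Q = 145 on 17 df, and the between-centre SD (DerSimonian-Laird) is 0.38.
- Subtracting the 224 screening diagnoses from the intervention counts: centre 16 becomes 25/74 = 0.34 and centre 15 becomes 31/19 = 1.63. Q = 125 and SD = 0.36.

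Most of the spread remains once the cases that screening found are taken out.

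**The case against.** The strongest reply is that Table I3 shows period effects and not response. Its 0.03 is a centre-by-period variance. With two periods per centre, that term and a centre-by-strategy term are aliased, so it mixes differences in response with local epidemic change. Starts were to be spread over about 30 days, and both the weekly period and its interaction with incidence had p < 0.0001, so epidemic change is a serious competitor. The subtraction in step 5 points the same way: at centre 16 only 2 of 27 intervention-period diagnoses came from screening, so 0.36 is not sensibly a response to screening. Centre 15 (49 of 80) is the clear exception. This reply stands, with the caveat that some screened cases might have been found by usual testing.

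A reader might therefore infer any of four stronger things, none of which the documents support:

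- That Table I3 establishes centre RRs of 0.6 to 1.6. It is only compatible with them.
- That the raw ratios of 0.36 to 4.2 are an upper bound on response variation. Unremoved calendar time can mask differences as well as inflate them, so these ratios bound nothing.
- That the SE of 0.07 against 0.04 measures the cost of omitting response variation. Table I3 also replaces weeks by a binary period, so the difference cannot be credited to one component. The dispersion ratio of 1.17 in the final model was read as no overdispersion.
- That the significant random effects in Table I2 contradict the sentence. Five of the six are centre intercepts, which describe level, and the sixth is a centre-by-period effect.

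Conversely, the 0.00 printed for centre-by-period variance in the final model does not show homogeneity. Table I2 gives a single coefficient for centre 11, so the term appears to be a per-week slope on another scale, and it is not a strategy term.

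It can also be said that section 1.5 meant the fixed period-by-strategy term as the replacement. That term describes whether the average effect differs between periods, not between centres, and it is absent from the later specification too.

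**Conclusion.** The clause that the response did not vary is unsupported. Table I6 (0.99 to 1.04) shows that no single centre drives the pooled RR, and nothing more. Homogeneity was neither tested nor shown, and the planned centre-by-strategy random effect was dropped without a stated reason.

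As to size, the data do not exclude centre RRs of about 0.6 to 1.6 (0.7 to 1.4 on the slope reading). That range rests on the rounded 0.03 of a sensitivity model, on normal random effects, and on reading all of the component as response, which cannot be justified with two periods per centre. No variation at all is not excluded either. It is not shown that the final model's interval is too narrow. The average conclusion does not depend on the disputed clause: Table I3, which carries an aliased form of the missing component, still gives 0.98 (0.84 to 1.15).

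**What to change.** - Delete the clause on the response to the intervention, and present Table I6 only as an influence check.
- Add the centre-by-strategy random effect of protocol 13.2 to the weekly, incidence-adjusted model in Changes to the analysis plan. Report its SD and a 95% prediction interval for a centre's RR, and say that it may still carry residual local epidemic change.
- State in the summary of changes why the term was removed.

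The cost is one more variance component, one reworded sentence and one line of documentation. With 18 centres the component may be poorly estimated or fall on zero, which should be reported as such and not as proof of homogeneity. The interval for the average may widen from 0.94 to 1.11 towards 0.84 to 1.15, with the null average conclusion likely unchanged.
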